#### Statistical analysis

The responses to the User Experience Questionnaire, assessing usability, will be analysed with summary statistics. We will examine any practice effects (temporal reliability) by checking for increasing correlation between the first test (in the research centre) and repeated tests (at home) using Kendall rank correlation coefficients. A Kendall rank correlation coefficient of ≥ 0.70 is considered strong; 0.50 to 0.69 as good; 0.30 to 0.49 as moderate and < 0.30 as poor. This will be tested separately for each participant’s device.

The outcome of study 2.2 will be a measure of the usability and reliability of TapTalk. Based on the results from this pilot study, we will make refinements to the software and/or instructions and then invite all ISLAND participants to complete the TapTalk at home as part of study 2.3.

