##### Study 2.2

We will undertake a prospective study of 50–100 (randomly selected) ISLAND Project participants who participated in Study 1, own a smartphone, and live within 30 km of the University of Tasmania research centre. They will be invited to attend the University of Tasmania Clinical Research Facility in Hobart for approximately 15 min and asked to bring their own smartphone. Participants will be asked to install the TapTalk app on their own smartphone and complete a consent form. Each participant will then complete the test protocol of hand and speech-like movements in front of the researcher. This will allow the researcher to observe if there are any issues around the usability of installing and operating the TapTalk app.

Each participant will be asked to complete a User Experience Questionnaire immediately after completing both tests, to further evaluate the usability of each form of the test (see supplementary files). We will invite participants to complete TapTalk on a smartphone at least three times at home over the next 7-day period, using the same device each time. They will be sent a reminder email every day over the 7-day period and asked to complete the TapTalk once each day if possible, or at least a minimum of 3 times in total. Their performance on each test will be automatically uploaded to a central secure TapTalk database.

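### Study 2.2 judges practice effects by a rising Kendall correlation per participant's device; a rise is neither necessary nor specific for practice, and read literally the per-device coefficient is undefined

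*Protocol article*

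**What the plan says.** All of this is in the Protocol article, Methods, Aim 2, Study 2.2 and its Statistical analysis.

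- **Sample:** "We will undertake a prospective study of 50–100 (randomly selected) ISLAND Project participants" who took part in Study 1, own a smartphone and live near the research centre.
- **Testing:** each participant installs the app on their own phone and does the first test at the centre, watched by a researcher. They are then asked to "complete TapTalk on a smartphone at least three times at home over the next 7-day period, using the same device each time", ideally daily.
- **Practice analysis:** the plan will "examine any practice effects (temporal reliability) by checking for increasing correlation between the first test (in the research centre) and repeated tests". These repeats are the home sessions, and the statistic named is Kendall's tau.
- **Interpretation:** tau is labelled strong from 0.70 upwards, good from 0.50, moderate from 0.30, and poor below that.
- **Unit:** "This will be tested separately for each participant’s device".
- **Output:** a measure of usability and reliability, used to refine the app and instructions before Study 2.3.

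No analysis of score level over the repeats (mean change, trend or agreement) is stated for Study 2.2.

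**The concern.** A practice effect is a change in the level of the score with repeated exposure. Kendall's tau uses only the order of participants, so it carries no information on a shift that everyone shares. The plan also names a direction, an increase, as the signal, and it equates practice with temporal reliability, which is a different quantity. The unit of analysis adds a second problem, since each participant uses one phone throughout.

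At stake is what Study 2.2 can report. It could describe TapTalk as reliable while scores drift from session to session. Study 2.3 then invites participants to four test points, admits anyone with two or more completions, and uses the 12-month score as predictor. That score can be a first, second or third attempt in that study, so exposure can differ between participants.

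**Working it through.** The protocol gives no power or precision figure for Study 2.2, so there is none to reproduce.

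**Inputs from the protocol:** 50–100 participants; one phone each; one centre test and at least 3 home tests; Kendall's tau with bands at 0.30, 0.50 and 0.70.

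**Assumed inputs, not in the protocol:** reliability of a single score (0.8, with 0.7 and 0.9 as a range) and size of gain (0, 0.3 and 1.0 SD per session). Step 1 needs neither.

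**1. Invariance.** Tau = (concordant pairs − discordant pairs) / all pairs, without ties. Adding a constant to every repeat score changes no ordering, so tau cannot move. In one simulated sample of 50, tau was 0.719 before a 2-unit gain was added to every repeat, 0.719 after it, and 0.719 after a monotone transformation.

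**2. Behaviour over three repeats.** Mean tau of first test with repeats 1, 2 and 3; 2,000 runs, n = 50, reliability 0.8:

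| Scenario | Tau at repeats 1, 2, 3 |
|---|---|
| No practice | 0.591, 0.590, 0.592 |
| Common gain 0.3 SD per session | 0.593, 0.591, 0.593 |
| Common gain 1 SD per session | 0.588, 0.588, 0.589 |
| Gain 0.3 per session, between-person SD 0.3, unrelated to baseline | 0.557, 0.480, 0.405 |
| No gain, noise shrinks | 0.630, 0.667, 0.693 |

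Results at n = 100 differ by no more than about 0.003. On the same data a paired comparison of repeat 3 with the first test rejected in about 100% of runs with a gain and in 4–5% without one.

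**3. Uneven gains can also raise tau.** For bivariate normal scores tau = (2/π)·asin(r). Take true-score SD 1, error SD 0.5, and a gain that grows with ability by 0.2 per session. Then r_k = (1 + 0.2k) / √{1.25 × [(1 + 0.2k)² + 0.25]}.

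- k = 1: r = 1.2 / √(1.25 × 1.69) = 0.826, tau = 0.62.
- k = 4: r = 1.8 / √(1.25 × 3.49) = 0.862, tau = 0.66.

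**4. Tau beside agreement.** Five sessions 0.25 true-score SD apart drift by 1 SD in total. The variance of the session means is 0.25² × 2.5 = 0.156. Absolute-agreement ICC = 1 / (1 + error variance + 0.156), with error variance = (1 − reliability) / reliability.

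| Reliability | Tau, with or without drift | ICC without drift | ICC with drift |
|---|---|---|---|
| 0.7 | 0.49 | 0.70 | 1/(1 + 0.429 + 0.156) = 0.63 |
| 0.8 | 0.59 | 0.80 | 1/(1 + 0.250 + 0.156) = 0.71 |
| 0.9 | 0.71 | 0.90 | 1/(1 + 0.111 + 0.156) = 0.79 |

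The protocol's label (moderate, good or strong in turn) is therefore the same with and without a 1 SD drift.

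**5. One device.** A single pair (first test, repeat) gives an undefined tau. One fixed first score set against 3 or 7 repeats is also undefined, because one variable is constant. Two other readings can be computed but are imprecise:

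- *Grouping by phone type:* the null SD of tau is √[2(2n + 5) / (9n(n − 1))], which is 0.41 at n = 5 and 0.25 at n = 10.
- *Correlating across tasks within a person:* with 3, 4 or 5 tasks the smallest two-sided exact p is 2/m! = 0.33, 0.083 or 0.017.

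**6. Centre against home.** The first test is always at the centre and every repeat at home, so a centre/home indicator is identical to a first-session indicator. Suppose pure practice with no setting effect and session means 0, 0.60, 0.70, 0.75, 0.78. The slope over the four home sessions is (−1.5×0.60 − 0.5×0.70 + 0.5×0.75 + 1.5×0.78)/5 = 0.059. The home term takes 0.7075 − 2.5×0.059 = 0.56. Most of the true learning would be labelled setting.

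**The case against.** The best defence has four parts.

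- **Rank stability is a recognised form of reliability.** Tau across 50–100 participants describes it properly. This stands, and tau can be kept for that purpose.
- **The device sentence may mean phone type.** Study 2.1 does analyse by type of smartphone, and each person does several tasks. The reading is possible, but it is not what Study 2.2 says. A reader might infer that the analysis is impossible. The protocol supports only that it is undefined on the literal wording and imprecise on the alternatives.
- **Study 2.3 is not harmed by a common gain.** A reader might infer that missed learning would there pass for preserved motor function. The protocol does not support this: decline is defined by CANTAB, and one TapTalk score, at 12 months, is the predictor. A gain common to all shifts only the intercept of that logistic regression and leaves the odds ratio unchanged. The remaining risk is unequal prior exposure at 12 months. Whether near-daily practice over a week carries over to 6-month intervals is unknown.
- **This is a pilot.** No pass/fail rule is attached to tau, and scores are stored centrally, so an analysis of level can be added. This lowers the severity, but does not make the stated rule correct.

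**Conclusion.** The point holds as a fault in a stated rule, not as missing detail. A rising tau is neither necessary nor specific for practice: common gains leave it flat, uneven gains move it either way, and shrinking noise raises it without any gain. It would go too far to say that tau never responds to practice, or that unequal gains always lower it; step 3 of the working shows a rise. On the literal wording the per-device coefficient does not exist.

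The invariance is exact and needs no assumption. The simulated and closed-form sizes, such as an ICC falling from 0.80 to 0.71 while tau stays at 0.59, depend on assumed reliability and gain. The consequence is that Study 2.2 could report reliability while scores drift. In Study 2.3 this matters only where prior exposure at the 12-month score differs between participants. Severity: should be fixed.

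**What to change.** Reword the Study 2.2 analysis as follows.

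1. **Practice:** fit a mixed model of each TapTalk score on session number with participant random effects. Take the trend from the home sessions and report mean change per session with 95% CI.
2. **Centre to first home test:** report this change separately and state that it mixes setting with first exposure. Do not rely on a centre/home term to separate them.
3. **Reliability:** report an absolute-agreement ICC and the standard error of measurement across participants. Keep Kendall's tau beside them as a description of rank-order stability, not as the practice check.
4. **Devices:** replace the per-participant device wording with phone type or operating system, as a descriptive subgroup.

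The cost is analysis wording only. The data and visits are unchanged, and mixed effects regression is already planned for Study 2.1. Separating setting from first exposure is not possible with the present design and is not promised by this change.

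### Study 2.2 measures reliability against an observed test at the research centre, so its coefficient reflects reproducibility across settings rather than test-retest reliability under like conditions

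*Protocol article*

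**What the plan says.** The Study 2.2 description (Aim 2) fixes the occasions. After installing the app at the Clinical Research Facility, "Each participant will then complete the test protocol of hand and speech-like movements in front of the researcher". Participants are then invited to "complete TapTalk on a smartphone at least three times at home over the next 7-day period, using the same device each time". Daily reminders follow, and they are "asked to complete the TapTalk once each day if possible, or at least a minimum of 3 times in total".

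The Statistical analysis section for Study 2.2 gives one analysis of the repeated scores. Its aim is given as "We will examine any practice effects (temporal reliability"). The method, with Kendall's coefficient as the statistic, is stated as "checking for increasing correlation between the first test (in the research centre) and repeated tests (at home"). The section then sets verdict bands: "A Kendall rank correlation coefficient of ≥ 0.70 is considered strong; 0.50 to 0.69 as good; 0.30 to 0.49 as moderate". Anything below 0.30 is called poor. The same section says that Study 2.2 will yield a measure of usability and reliability, and that software or instructions will be refined before all ISLAND participants are invited to test at home in Study 2.3.

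The article describes no second centre test, no alternation of settings and no comparison of one home test with another.

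**The concern.** A test-retest coefficient is meant to show how well a score repeats when only the occasion changes. Here two things change between the members of every pair: the occasion, and the setting together with the researcher's presence. If some people do relatively better when watched at the centre and others do relatively better at home, that reordering lowers the coefficient and is counted as unreliability of the test.

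Study 2.3 has participants use TapTalk at home or in a place of their choice. Reliability under home conditions is therefore the quantity closest to that use, and the stated analysis never estimates it, although each participant is asked for at least three home tests on the same device. The bands make the level matter, because the coefficient will be reported as strong, good, moderate or poor.

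A narrower concern is practice. The gain from first exposure falls between the first and second tests, which is also the step from centre to home, so the two cannot be separated at that step.

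**Working it through.** The documents give no sample-size calculation, variance or expected coefficient for this analysis, so there is no figure to reproduce. The check has a structural part and an illustrative calculation.

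**Structure**

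| Occasion | Setting | Researcher watching | Role in the stated analysis |
|---|---|---|---|
| 1 | Research facility | Yes | Reference for every coefficient |
| 2, 3, 4 and later | Home | None described | Each compared with occasion 1 |

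Occasion 1 versus any later occasion is centre versus home in every participant. Among the later occasions the setting is constant.

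**Model (all variances assumed)**

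Score = person + person-by-setting + error. Person variance is 1, the person-by-setting variance is s² (independent for centre and home, and shared by all of a person's home tests), and the error variance is e².

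- Centre-home correlation: ρ = 1 / (1 + s² + e²)
- Home-home correlation: ρ = (1 + s²) / (1 + s² + e²)
- For bivariate normal scores: tau = (2/π) × arcsin(ρ)

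**Results with e = 0.6 (e² = 0.36)**

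| s | Total variance | Centre-home ρ | Centre-home tau | Home-home ρ | Home-home tau |
|---|---|---|---|---|---|
| 0 | 1.36 | 1/1.36 = 0.735 | 0.53 | 0.735 | 0.53 |
| 0.3 | 1.45 | 1/1.45 = 0.690 | 0.48 | 1.09/1.45 = 0.752 | 0.54 |
| 0.6 | 1.72 | 1/1.72 = 0.581 | 0.40 | 1.36/1.72 = 0.791 | 0.58 |

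With s = 0.3 or 0.6, the home-home value lies in the plan's good band and the centre-home value in its moderate band. Simulation with 75 participants, inside the planned 50 to 100, agrees with these figures.

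**Other assumed values**

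| s | e | Centre-home tau | Home-home tau | Bands |
|---|---|---|---|---|
| 0.3 | 0.5 | 0.54 | 0.60 | both good |
| 0.3 | 0.7 | 0.44 | 0.48 | both moderate |
| √0.2 | √0.1 | 0.56 | 0.75 | good against strong |

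With s = 0.6, the gap runs from 0.29 (e = 0.3) down to 0.14 (e = 0.8).

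**Trend over home tests**

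With s = 0.3, e = 0.6 and no practice effect, the simulated centre-home tau for home tests 1, 2 and 3 is flat at about 0.48. A shift of the same size for everyone leaves tau unchanged, because ranks do not move.

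**First-to-second step**

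In simulation with e² = 0.1, a setting shift of 0.3 SD alone and a first-step practice gain of 0.3 SD alone each gave a mean change of +0.30. Equal and opposite amounts of the two gave 0.00. The data at that step cannot say which occurred.

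**The case against.** Four points can be made for the plan.

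1. **Practice is sought as a trend over the home tests, where setting is constant.** This stands. A reader might infer that occasion is wholly confounded with setting, or that a setting effect would pass for practice in the planned analysis. The documents do not support either reading. Occasion varies within one setting over at least three home tests, a stable setting effect leaves the series flat, and a uniform shift leaves tau unchanged. The article plans no first-to-second mean contrast, so the aliasing of mean changes limits what can be learned but does not bias a planned result.

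2. **Centre-home agreement is useful in its own right.** This also stands. In Aim 3 a research assistant or researcher is present and may hold the phone, and Study 2.3 allows settings other than home. The coefficient answers a real question, though a different one from test-retest reliability under like conditions.

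3. **The size is assumed.** True. The change of band at s = 0.3 depends on e = 0.6 placing tau near the 0.50 edge, and the gap of 0.06 there is about one standard error of a single tau at 75 participants. No document supports a particular setting variance. The direction does not depend on the values chosen: under this model any person-by-setting variance puts centre-home below home-home.

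4. **This is a pilot in a condensed article, with no pass mark tied to the bands.** This limits the consequence. It does not remove the point, because the article itself names the reference test, the statistic and the bands, and that stated reference is what is at issue. That the home tests are unwatched is a fair reading of the text rather than its wording.

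**Conclusion.** The point holds in a limited form. Every stated coefficient in Study 2.2 is anchored on the observed centre test, so it mixes test-retest error with the change of setting and supervision. If setting effects differ between people, it understates home-to-home reliability. Under the assumed variances (person SD 1, error SD 0.6), the shortfall in tau is about 0.06 with a person-by-setting SD of 0.3 and about 0.19 (0.395 against 0.581) with 0.6. Either is enough to move the label from good to moderate. With other error SDs the label may stay the same, and with no setting component there is no shortfall.

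On practice, the only loss is at the first-to-second step, where first-exposure gain and the move home cannot be told apart. The weakness lies in the choice of reference and not in the data collection, since the planned home tests already allow a like-for-like estimate. It is worth correcting before the analysis, but it does not threaten the study.

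**What to change.** In the Statistical analysis section for Study 2.2:

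- Estimate test-retest reliability, and any trend over sessions, from the home tests, with home test 1 as the reference (home 1 versus 2, 1 versus 3, and so on).
- Report the centre test versus home test 1 beside this, labelled as agreement across settings plus first exposure.
- State which of the two coefficients the verdict bands are applied to.

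The cost is a change of wording and a little extra analysis. No new visits, tests or participants are needed. The small downside is that the home-only trend leaves out the first-exposure gain. The separate centre-home contrast still includes it, though mixed with the change of setting.

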##### Study 2.3

We will undertake an 18-month prospective study of approximately 1,000 ISLAND Project participants who have completed online cognitive CANTAB tests in 2021. Participants in the ISLAND Project [45, 46] are invited to complete online CANTAB cognitive tests every 2 years. The first testing period was mid-2021 and ∼3,000 participants completed the tests; these participants will be invited to take part in the TapTalk prospective validity study. Every 6 months over an 18-month period (four data collection points in total; T0, T + 6, T + 12, T + 18), eligible participants will be invited via the ISLAND Project website (‘portal’), to complete TapTalk at any time over the next one-month period. Participants will be asked to complete TapTalk on their own smartphone at home or in a setting of their choice. Consent will be taken at each data collection point. When participants complete the TapTalk app they will be asked to complete a questionnaire about user experience and symptoms relating to hand and speech function (see supplementary files). The whole procedure, including the questions and tests, is expected to take about 5 min. A reminder email will be sent 1, 2 and 3 weeks after the initial invitation to people who have not yet completed the test.

#### Statistical analysis

The data from participants who complete TapTalk on two or more occasions over an 18-month period, and CANTAB on two occasions (2021 and 2023) will be included in the analysis. De-identified ISLAND Project participants will be classified as cognitively ‘stable’ or ‘declining’ using longitudinal CANTAB cognitive scores. TapTalk scores will be calculated using algorithms developed in Study 1. Logistic regression will be used to estimate the odds of a participant being confirmed as ‘declining’ at time T_2_ (24 months) conditioned on TapTalk score at time T_1_ (12 months). The overall outcome of Study 2 will be a smartphone app, TapTalk, that is usable, reliable and validated against established online CANTAB cognitive tests.

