##### Inclusion criteria

Adults ≥ 50 years old who are (i) participants in the ISLAND Project [45] (ii) have provided a blood sample for analysis of blood-based biomarkers, (iii) have *normal* cognition defined as not ≥ 2 SD above the mean total errors (adjusted for age) on the CANTAB PAL tests, and (iv) have no history of persistent cognitive symptoms reported on ISLAND Project questionnaires (all participants are asked each year: *Have you noticed a substantial change in your memory and mental function in recent years*? [YES/NO], *Have you been told by a doctor that you have dementia?* [YES/NO], *Have you been told by your doctor that you have a memory impairment but they were uncertain if you have dementia?* [YES/NO], *Have you discussed concerns about your memory and mental function with your doctor or other health professional?* [YES/NO]).

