### Sample size justification

Using CANTAB cognitive test responses already collected in the ISLAND Project (n = 3,000), we estimate that we will collect > 1,000 complete cases (TapTalk app completion twice in 18 months and CANTAB at baseline and 24 months), which is ample for logistic regression with a single fixed-effect predictor variable.

### AIM 3

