If any unexpected adverse events (an unforeseen harmful, unpleasant or undesirable response, reaction or outcome experienced by a research participant or researcher) or serious adverse effects occur, these will be documented, reported in line with Good Clinical Practice, and appropriate referrals made for care. A participant may be discontinued from the study at any time if the participant or the research team feels that it is not in the participant’s best interest to continue. Possible reasons for discontinuation include participant withdrawal of consent, lost to follow-up, or new co-morbidity/diagnosis that would meet the exclusion criteria (e.g., loss of hand function). If the participant has taken part in completing TapTalk, and then changes their mind after data collection, the research team will do their best to withdraw all data from the study but if their de-identified data has already been included in the group analysis. it will not be possible to withdraw this data. Reasonable attempts will be made by the research team to provide a reason for participant withdrawals in data collection.

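### Study 2.3 picks its analysis set by later completions, a rule that does not match its own model and may distort the estimated odds of decline if decliners return less often

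*Protocol article*

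**What the plan says.** Under Aim 2, the statistical analysis section for Study 2.3 states the analysis set in these terms: "The data from participants who complete TapTalk on two or more occasions over an 18-month period, and CANTAB on two occasions (2021 and 2023"). The Aim 2 sample size justification repeats the rule and rests on it: "we estimate that we will collect > 1,000 complete cases". The pool is the roughly 3,000 people who took CANTAB in 2021; "these participants will be invited to take part in the TapTalk prospective validity study".

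The outcome, stable or declining, is assigned "using longitudinal CANTAB cognitive scores", and no other source is named. The model is then described: "Logistic regression will be used to estimate the odds of a participant being confirmed as" declining at 24 months, "conditioned on TapTalk score at time" T1, given as 12 months. TapTalk is offered at four points: T0, T+6, T+12 and T+18.

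Two other places bear on this. The Aim 1 inclusion criteria describe yearly ISLAND questions on memory change and on a doctor's diagnosis of dementia or memory impairment ("all participants are asked each year"). The Data management section lists "lost to follow-up" among possible reasons for discontinuation.

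**The concern.** Two separate matters arise.

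The first is a mismatch between the inclusion rule and the model. The model needs a baseline CANTAB, one TapTalk score at a named time and a second CANTAB. The rule asks for something else, a count of TapTalk completions, and so admits people the model cannot use and excludes people it can.

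The second is selection on follow-up. The outcome exists only for people who come back and complete an online cognitive battery. In a study of cognitive decline, decline is itself a plausible reason not to come back. The article names the odds of decline as the quantity to be estimated, and those odds are sensitive to outcome-related loss. The association between score and decline, which carries the claim that TapTalk is validated against CANTAB, is sensitive only under narrower conditions.

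**Working it through.** **The plan's own figure.** The expected number above 1,000 cannot be reproduced, because the article gives no uptake, dropout or decline rate. It implies only that 1,000 / 3,000 = 33% of those invited are analysed. The other 2,000 mix people who never start with people who stop, in unknown proportion, so 67% is not an attrition rate.

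**Step 1: the rule against the model.** This takes the 12-month score as one of the four collection points.

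| Person | Two completions? | Has 12-month score? | Both CANTABs? | Under the rule | Usable in the model? |
|---|---|---|---|---|---|
| Tested at T+12 only | No | Yes | Yes | Dropped | Yes |
| Tested at T0 and T+6 only | Yes | No | Yes | Included | No |

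Two completions out of four points can fall in 6 ways, and 3 of those 6 omit any given point. Two completions are therefore neither necessary nor sufficient. This step needs no assumption about dropout.

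**Step 2: effect of loss on the odds.** Let r1(x) and r0(x) be the probabilities that a decliner and a stable person with score x are retained. Then

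observed odds at x = true odds at x × r1(x) / r0(x).

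Illustration (all inputs assumed): 15% truly decline; 50% of decliners and 70% of stable people are retained.

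- Observed rate = 0.15×0.50 / (0.15×0.50 + 0.85×0.70) = 0.075 / 0.670 = 11.2%.
- Odds factor = 0.50 / 0.70 = 0.71.
- With decliners retained at 35%: rate 0.0525 / 0.6475 = 8.1%, odds factor 0.50.

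Range over assumed true decline rates and retention ratios (observed rate):

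| True decline | Ratio 0.9 | Ratio 0.75 | Ratio 0.5 |
|---|---|---|---|
| 5% | 4.5% | 3.8% | 2.6% |
| 10% | 9.1% | 7.7% | 5.3% |
| 20% | 18.4% | 15.8% | 11.1% |

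**Step 3: effect on the TapTalk odds ratio.** By the same identity, the odds ratio changes only if r1(x) / r0(x) changes with x. Simulation with 3,000,000 records, about 10% declining, true odds ratio 2.0 per SD (a higher score meaning higher risk) and about one third retained:

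| Loss depends on | Odds at mean score, estimated / true | Odds ratio per SD |
|---|---|---|
| Nothing | 1.00 | 1.99 |
| Score only | 0.99 | 2.00 |
| Decline only, decliners retained half as often | 0.50 | 2.00 |
| Decline and score, additive on the logit scale | 0.56 | 1.86 |
| Decline by score, high-risk decliners lost most | 0.55 | 1.33 |
| Decliners retained 1.25 times as often | 1.25 | 2.00 |

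**Step 4: would weighting on measured variables remove it?** A rerun of the two joint-loss rows with a fresh random sample, weighting by the inverse probability of retention given score, left the odds factors at 0.56 and 0.55. The odds ratios were 1.85 before and 1.86 after in the first, and 1.33 before and after in the second. Weighting on score alone does not cure loss caused by decline itself.

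**The case against.** The strongest reply is that nothing in the article shows decliners returning less often. Aim 2 is described as being in cognitively asymptomatic adults, follow-up is about two years, reminders are planned for TapTalk, and loss to follow-up is only listed as a possible reason for discontinuation across all studies. If worried decliners return more often, the odds are biased upwards. The odds ratio, which matters most for validation, is untouched when loss depends on decline alone. A condensed article may also leave imputation and sensitivity analyses to a document not shown.

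Most of this stands. A reader might infer that the odds of decline are certainly biased downwards, or that two thirds of the cohort drop out. The documents support neither: there are no return rates by cognitive status, and the uncounted 2,000 include people who never take part.

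It is also fair that the ISLAND surveys are online, so some non-returners will not answer them. Scoring a reported diagnosis as decline only in people without the second CANTAB would create a second outcome definition in a study meant to validate against CANTAB.

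What does not stand is the appeal to an unseen plan on the analysis set itself. The article states a completers-only rule and sizes the study on it; an analysis plan that did otherwise would contradict it. The mismatch in Step 1 does not depend on dropout at all.

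**Conclusion.** The concern holds in a limited form. The two-completion requirement is a definite misfit with a model that uses one TapTalk score, and this follows from the article alone. The bias is conditional. If decliners return for the second CANTAB less often than stable people with the same score, the estimated odds of decline are too low by exactly the ratio of the return rates: 0.71 at an assumed 50% versus 70%, and between 0.90 and 0.50 over the range of ratios tabulated. The TapTalk odds ratio is diluted only when loss depends on decline and score in combination; in the assumed scenarios, a true 2.0 became 1.86 or 1.33. Direction and size rest on assumptions that the article neither supports nor rules out. The change is still worth making, because Study 2.3 carries the claim of validity against CANTAB and the repair uses data already being collected.

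**What to change.** - **Analysis set.** Define it as everyone with the 2021 CANTAB and the 12-month TapTalk score, and remove the requirement for two completions.
- **Description.** Compare people with and without the second CANTAB on baseline CANTAB, age, education and TapTalk score.
- **Missing outcomes.** Use multiple imputation or inverse-probability weighting, with baseline CANTAB, age, education and the annual ISLAND memory and diagnosis answers as auxiliary variables alongside the TapTalk score.
- **Sensitivity.** Add a missing-not-at-random analysis, since measured variables may not explain loss caused by decline. Include one version that scores non-returners with a newly reported dementia or memory-impairment diagnosis as declining. Keep this out of the main analysis so that the main outcome stays CANTAB-based.
- **Reporting.** Show the completers-only model next to these.

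The cost is a change of wording and modest extra analysis, with no new data collection. The drawback is that the main result then rests on a stated missing-data model.
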